**Hypotheses**

1. Consumption of whole milk (2 × 500ml; 2 × ~20g protein) after a RE session twice a week over the period of 6 weeks post-randomisation is feasible as an intervention in older adults (aged ≥65) who may be at risk of sarcopenia.
2. The intervention is acceptable with good compliance, low attrition, and no adverse health effects, including appetite suppression, negative dietary changes, muscle damage and soreness.

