# Primary and secondary outcomes of the study

Primary outcome measures

1. Feasibility and acceptability of the intervention (Time frame: 6 weeks post-randomisation and baseline assessment).
2. Measures to include: applicability, dosage and duration of the intervention, compliance, attrition, and adverse health effects such as appetite suppression, dietary changes and muscle soreness (Time frame: 6 weeks post-intervention).

Secondary outcome measures for exploratory analyses

1. Difference in physical performance measures: Short Physical Performance Battery^26^ (balance, 4m-gait speed, 5-chair stands) (Time frame: at baseline and after 6 weeks of intervention).
2. Difference in muscle strength measure: maximum strength test^27^ (grip strength, GS; Jamar hand-held 5030J1 dynamometer) (Time frame: at baseline and after 6 weeks of intervention).
3. Difference in muscle mass measure: Bioelectric Impedance Analysis (BIA; Tanita MC-780MA Body Composition Analyzer) (Time frame: at baseline and after 6 weeks of intervention)^28^.
4. Difference in self-reported quality of life measure: SF-12 (Time frame: at baseline and after 6 weeks of intervention)^29^.
5. Difference in activities of daily living measure: Barthel Index^30^.

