Milk / control drink will be consumed as a bolus intake of 500ml under the supervision of a researcher immediately after exercise over 40-50 minutes during the recovery period (or longer if needed). Participants will be advised to resume their usual diet. Second dose of 500ml will be consumed at participants’ home over the next 4-5 hours. All drinks consumed at home will be clearly labelled as either ‘MIlkMAN study milk’ or ‘MIlkMAN study juice’. Second dose of 500ml can be consumed with other foods as a part of their usual diet (e.g. tea, cereal, mushed potatoes, etc.). Participants will be contacted by phone in the evening to check for muscle soreness and compliance with milk/ control drink consumption. Each participant will be provided with a plastic measuring jug (500ml) and a log sheet to measure and record milk/control drink consumption at home and to report it back to a researcher conducting the phone call.

On average, 500ml milk contains ~20g of protein needed to stimulate muscle protein synthesis above stimulation provided by RE. Whole (cow) milk (nutritional estimates of 22 UK samples during winter and summer) provides 66 kcal/100g of energy^44^. Fresh milk will be provided by Arla® (Nutrition Specialist: [name] at Arla Foods). Arla Cravendale® whole milk contains 3.6g fat, 3.4g protein, and 4.7g of carbohydrates per 100g of milk. Arla Cravendale® skimmed milk contains 0.3g fat, 3.6g protein, and 4.9g of carbohydrate per 100g of milk. Energy of control drink (cranberry juice; Ocean Spray Classic) will be balanced to match whole milk energy content and supplemented with maltodextrin (e.g. cranberry juice (45kcal/100g of energy^44^) will be supplemented with 6.05g of maltodextrin (3.8kcal/g) per 100g of juice; 1tsp = 15kcal; 30.25g for 500ml of juice).

Milk and control drink storage and handling

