4. Dietary intake: 24-hr dietary recall (Intake24 (https://intake24.co.uk/) multi-pass, computerised 24-hr recall supported by the Newcastle University)
5. Appetite assessment: a 4-item Simplified Nutritional Appetite Questionnaire
6. General health and functioning: Self-reported quality of life: SF-12; Activities of daily living: Barthel Index; blood pressure (systolic and diastolic)

Participants’ feedback will be collected at the end of follow-up assessment using a combination of structured multiple-response and standardised open-ended questions to explore the following themes:

1. Attitudes and barriers of 2 × 500ml milk intake post-exercise (e.g. volume of liquid, taste, etc.)
2. Their opinion about milk as a functional food for muscle strength/ function
3. Appetite changes, changes in habitual diet because of milk/ control drink intake
4. What they liked and disliked about the study (intervention).

The follow-up visit will be completed within 50 minutes.

Muscle mass (body composition), appetite assessment (a 4-item Simplified Nutritional Appetite Questionnaire), dietary intake (24-hr dietary recall) and blood pressure will be assessed at the last (12^th^) intervention visit during the 45 minutes recovery period at The Parks.

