There is also a small risk of gastrointestinal discomfort and possible unknown milk allergies (lactose or milk proteins). Participants who report any significant discomfort associated with milk or control drink intake (e.g. nausea, indigestion, diarrhoea, etc.) will be excluded from the study. In addition, there is a small risk of metabolic changes and weight gain due to the consumption of 650 kcal from whole milk and control drink (2 × week over 6 weeks) which will be counteracted by the increased energy expenditure during the RE programme. Appetite will be assessed at baseline and post-intervention, and total energy intake will be estimated using the Intake24 (computerised 24-hr dietary recall) pre- and post-intervention to examine any changes in energy intake. Also, weight and body fatness will be estimated using the Tanita Body Composition Analyzer at baseline and after the intervention.

There is also a small risk of falling during the walking test. However, the attending researcher will assess individual risk at the point of data collection (re-check exclusion criteria and endurance of consent) and omit measurements/ test if they felt it unsafe or that capacity to consent is not present or consent does not endure. It is made clear to participants that they are free to withdraw at any time. Should a decision to withdraw from the study be made, a reason for the withdrawal will be recorded. However, participants can withdraw without providing any explanation.

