**Appendix 3**

Visual analogue scale for muscle soreness

[figure not shown]

0 = no pain, 1-3 = mild pain, 4-6 = moderate pain; 7-10 = severe pain

**Instructions for participants** (explained to participants by a researcher)

- This is a Visual Analogue Scale. The scale describes the intensity of your pain, 0 meaning no pain at all, 1 to 3 meaning mild pain, 4-6 moderate pain, and 7-10 the worst pain.
- Assessment ~45 minutes after exercise: Which number on the scale describes the best your muscle soreness in your (i) arms and (ii) legs?
- *Assessment in the evening over the phone (6-7 hours after exercise)*: A researcher will call you in the evening after each visit to the Parks to ask you again about your muscle soreness in your arms and legs. Please use the visual analogue scale that we gave you to rate your muscle soreness in your (i) arms and (ii) legs.

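### Gastrointestinal and allergic symptoms are named risks of the drink, but no scheduled contact is described as asking about them

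*Protocol*

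**What the plan says.** The Protocol section on ethical considerations, risk and burden names the hazard: "There is also a small risk of gastrointestinal discomfort and possible unknown milk allergies (lactose or milk proteins". It then sets a consequence that depends on the participant's own report: "Participants who report any significant discomfort associated with milk or control drink intake (e.g. nausea, indigestion, diarrhoea, etc.) will be excluded from the study".

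Adverse effects belong to the primary objective. Hypothesis 2 reads "The intervention is acceptable with good compliance, low attrition, and no adverse health effects, including appetite suppression, negative dietary changes, muscle damage and soreness". The primary outcome measures refer to "adverse health effects such as appetite suppression, dietary changes and muscle soreness". Neither list names gastrointestinal symptoms, but the second is open-ended.

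Under Data collection (Milk and control drink intake), the first 500 ml is drunk under supervision after exercise and the second at home over 4-5 hours. The evening call is described thus: "Participants will be contacted by phone in the evening to check for muscle soreness and compliance with milk/ control drink consumption". The question put in that call is given in Appendix 3: "Which number on the scale describes the best your muscle soreness in your (i) arms and (ii) legs".

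**The concern.** The study asks whether 2 × 500 ml of milk after exercise is feasible and acceptable to older adults, and whether the results can inform a larger trial. How well the drink is tolerated is central to that. Exclusion criteria remove self-reported lactose intolerance, milk allergy and diagnosed gastrointestinal disease, so what remains is mainly unrecognised intolerance, which appears only once drinking starts.

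The protocol sets out what each contact covers, and none of the descriptions includes these symptoms. If the plan is followed as written, they are collected by passive report. This is a matter of data collection, so no later analysis can recover what was not asked. A report of no or few gastrointestinal effects could then mean good tolerance or simply no question.

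**Working it through.** **Step 1. Contacts set side by side.**

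| Contact | Content described | Gastrointestinal or allergy item |
|---|---|---|
| Each exercise session (Resistance exercise programme) | Blood pressure, heart rate, perceived exertion, muscle soreness | None |
| Evening call (Milk and control drink intake; Appendix 3) | Soreness in arms and legs, drink consumption | None |
| 12th gym visit, additional assessments | Body composition, blood pressure, diet recall, appetite | None |
| Post-intervention home visit | Physical performance, grip strength, SF-12, Barthel Index | None |
| Feedback at the end of that visit | Barriers to the drink, opinion of milk, appetite and diet change, likes and dislikes | Not named; could emerge |

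**Step 2. Which listed adverse effects are actively asked about.** Appetite is covered by questionnaire and diet by 24-hour recall, both before and after the intervention. Soreness is scored after every session and again by phone. These are solicited. Gastrointestinal and allergic symptoms are not described as solicited.

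**Step 3. Volume.** Two sessions a week for 6 weeks is 2 × 6 = 12 sessions and 12 evening calls per participant. If all 30 complete, that is 30 × 12 = 360 calls and 360 × 2 = 720 doses, of which 360 are taken at home.

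**Step 4. Timing of the call.** I assume that the 4-5 hours for the home dose start when the first drink is finished. With 40-50 minutes for the first drink, the second is finished between 40 min + 4 h = 4 h 40 min and 50 min + 5 h = 5 h 50 min after exercise. Appendix 3 places the call at 6-7 hours. The call can therefore come as little as 10 minutes (6 h − 5 h 50 min) and at most 2 h 20 min (7 h − 4 h 40 min) after drinking finishes at those limits. Later symptoms could be picked up only at the next session.

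**Step 5. What a low count would mean (illustration).** The protocol states no figure on this point, so there is none to reproduce. Let *p* be the true proportion of participants with symptoms and *s* the share of those affected whose symptoms are recorded. Both are assumptions. The chance of recording at least one case among *n* participants is 1 − (1 − *p*·*s*)^*n*. For the two milk arms together, *n* = 20:

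| True rate *p* | *s* = 1.0 | *s* = 0.5 | *s* = 0.3 |
|---|---|---|---|
| 5% | 64% | 40% | 26% |
| 10% | 88% | 64% | 46% |
| 20% | 99% | 88% | 71% |

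For example, 1 − 0.90^20 = 0.878 and 1 − 0.95^20 = 0.642. In a single arm of 10 at *p* = 10%, the three values are 65%, 40% and 26%.

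**Step 6. What a zero count would exclude.** With full capture, no cases among 20 gives a one-sided 95% upper bound of 1 − 0.05^(1/20) = 13.9% (25.9% for *n* = 10, 9.5% for *n* = 30). With capture *s*, the bound applies to *p*·*s*. At *s* = 0.5 the bound on *p* is 13.9% / 0.5 = 27.8%. Since *s* is unknown under passive report, no bound on the true rate can be given.

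**The case against.** The best defence is that the protocol is not silent on safety. The exercise physiologist is to monitor other health risks. Signs of excess discomfort are to be assessed regularly. All adverse events go on the case report form, and unfavourable symptoms count as such. A researcher watches the first drink, and the evening call reviews home consumption, so an unfinished dose invites the question why. A reason for withdrawal is recorded where the participant gives one. The final feedback covers "Attitudes and barriers of 2 × 500ml milk intake post-exercise (e.g. volume of liquid, taste, etc" and includes open-ended questions. The case report form and call script are not shown and may contain a symptom list.

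Part of this stands. It cannot be said that nobody will ask, only that no contact is described as asking. The general provisions do not close the gap, however. Excess discomfort is to be assessed by visual analogue scale, in the paragraph on exercise risk, and the scale in Appendix 3 concerns arms and legs. The adverse event section says what is recorded, not how it is elicited. The feedback comes once, after the intervention, and may not reach participants already excluded for discomfort, who might also be replaced from the reserve list.

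A reader might infer that the whole expectation of no adverse effects rests on spontaneous reports. It does not: the effects that Hypothesis 2 lists are largely solicited (Step 2). Nor is asking about soreness twice misplaced, because the rationale expects milk to reduce soreness, which makes it a relevant comparison between arms.

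**Conclusion.** The point holds in a limited form. Only the gastrointestinal and allergy component of the adverse-effects outcome relies on participant-initiated reports, apart from one non-specific late feedback theme. Nothing is contradicted or miscalculated, and no sample size or power figure is affected, since the protocol claims no power.

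The size of the loss cannot be derived from the documents. The percentages in Steps 5 and 6 rest on assumed symptom rates and capture shares, and the protocol itself calls the risk small. What they show is the direction: incomplete capture makes a zero or low count more likely without better tolerance.

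Two further inferences are tempting but unsupported. That the exclusion rule discourages reporting is plausible, but nothing in the protocol shows it. That participants with milder symptoms continue drinking is not a failure of the rule, which covers only significant discomfort.

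The change is still worth making, because it is cheap and the missing information cannot be obtained afterwards.

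**What to change.** Add a fixed short item on gastrointestinal and allergic symptoms (for example nausea, bloating, indigestion, diarrhoea, rash), graded none, mild, moderate or severe, together with one open question about any other problem. Ask it in the existing evening call and again at the next session's pre-exercise check, to cover symptoms that begin after the call. For the 12th session, the post-intervention home visit can serve as the second occasion. Use identical wording in all three arms.

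Name these symptoms in the adverse-effects primary outcome. Report, by arm, the number of participants with any symptom and the number excluded for drink discomfort, including anyone later replaced from the reserve list. If the case report form or call script already contains such an item, a sentence in the protocol saying so is enough. The exclusion rule itself stays as it is.

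The cost is one or two lines on existing forms and about a minute per contact, with no new visit or staff. More mild symptoms will be recorded, so the tolerability figure will look slightly less favourable.

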This pilot study will recruit 30 older adults aged 65 and over (≥65) who live in the community We will include individuals who have no known milk allergies and do not currently participate in structured gym program, and meet other inclusion and exclusion criteria as reviewed through their registering general practice within North East and North Cumbria Clinical Research Network, North East England. Eligible individuals will be randomly assigned to one of 3 groups: (group 1) ‘whole milk + RE’, (group 2) ‘skimmed milk + RE’, and (group 3) ‘control drink + RE’ (juice with added carbohydrates to adjust for energy in whole milk). Each 500ml of milk provides about 20g of protein. Participants in each group will receive a home visit from a trained researcher to complete sociodemographic and health questionnaire and functioning assessment over a period of 6 weeks (approximately). Next, they will complete a 6-week intervention (milk/ control drink + RE) twice a week at a sports/recreation centre under the supervision of an exercise physiologist. Right after exercise, participant will consume 500ml milk/ control drink within 40-45 minutes (supervised), and another 500ml at home over the next 4-5 hours (unsupervised). Another home visit will be conducted after the intervention is completed over a 3-4 week period (approximately), and will include similar health and functioning assessments from the first home visit, and will also gather participant views about participating in the study.

Study aims:

(i) Feasibility and acceptability of (whole) milk in combination with resistance exercise as an intervention to increase muscle function (physical performance), strength and mass in community-dwelling older adults aged ≥65 who may be at risk of sarcopenia. We will ask:

- Is an intervention of 2 × 500ml milk + RE twice a week for 6 weeks feasible?
- Is an intervention of 2 × 500ml milk + RE twice a week for 6 weeks acceptable to community-dwelling older adults?

(ii) To explore whether consumption of milk (whole and skimmed) in combination with RE has an influence on physical performance, muscle strength, muscle mass, self-reported quality of life, and activities of daily living in community-dwelling older adults who may be at risk of sarcopenia compared to control group (juice supplemented with carbohydrates + RE)?

(iii) To provide important information for planned future research.

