The loss of muscle mass and strength associated with ageing is further accelerated by acute and chronic stressors such as disease, physical inactivity, reduced mobility, and poor diet. Adequate intake of dietary protein (essential amino acids; EAA) from animal and plant sources in combination with resistance exercise (RE) are recognised as key modifiable factors in muscle ageing and physical decline^10,11^. Intervention studies that examined a combined effect of protein (EAA) supplements and RE to stimulate muscle protein synthesis (MPS) have observed an increase in total muscle protein by protein intake within 3-5 hours after exercise in both young and older adults^12^. Older adults experience a blunted response after protein ingestion to stimulate MPS, especially to lower amounts of protein (EAA) of <20g (<10g) compared with young adults. It has been shown that greater amounts of protein supplementation and periodic feeding in combination with repeated bouts of RE may results in increased muscle mass in older adults diagnosed with frailty and sarcopenia^13-15^.

However, current research lacks in understanding the role of whole foods (e.g. milk and dairy products, fish, and meats) in the prevention of sarcopenia in older adults, although the importance of a ‘whole food approach’ and the combined effects of nutrients within foods on health and functioning is well recognised^16^. Regular consumption of high quality, nutrient-dense foods, rich in macro- and micronutrients relevant for muscle health^17^ within a varied diet may provide a platform for developing strategies for maintenance of muscle strength, mass and function in older adults that do not include drugs, supplements and medical products.

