Milk (cow) is an example of whole foods which may have potential to slow down and prevent muscle wasting. Whole milk is a source of high-quality proteins (6.3g/l (20%) of soluble whey proteins and 26g/l (80%) of insoluble caseins), minerals (e.g.1200 mg/l of calcium, 950 mg/l of phosphorus, 120 mg/l of magnesium), vitamins (fat-soluble A, D, and E and water-soluble B vitamins and vitamin C), bioactive lipids and fatty acids of which 30% are (mono and poly) unsaturated and 70% saturated fatty acids^18^. Whey protein supplements are considered superior to other protein sources to stimulate MPS after exercise in young and older adults^19^. Furthermore, intake of milk fats in whole milk increased the use of EAA for muscle protein synthesis after exercise in young men compared to fat-free milk^20^, suggesting additional benefits of milk lipids for muscle. Other benefits of milk (with milk fat) for muscle health include the reduction in exercise-related muscle damage, soreness, and decline in muscle performance in young adults^21^. Therefore, in addition to proteins, whole milk contains valuable minerals, vitamins, carbohydrates and milk fats (a delivery medium for fat-soluble vitamins A, D and E)^18^, and their ratio may be important for ageing muscle. Studies comparing the impact of low-fat versus whole milk providing >20g protein/day after exercise on muscle mass and function in older adults are lacking.

Milk and dairy product have other health benefits as an important part of a healthy diet across the life course, being crucial not only for the maintenance of bone density, but also associated with a reduced risk of adverse health outcomes, including diabetes, cardiovascular diseases, dementia, micronutrient deficiency, and obesity.

Taken together, whole milk (a functional food) in combination with RE could be beneficial for muscle health and function in older adults at risk of sarcopenia, and an important part of sarcopenia prevention in later life. Therefore, the main aim of this study is to explore the feasibility and acceptability of such an intervention in relation to physical performance, muscle strength and mass in community-dwelling older adults who may be at risk of sarcopenia.

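### The protocol's own product composition gives about 17.0–17.6 g (whole) or 18.0–18.6 g (skimmed) of protein per 500 ml, not the stated ~20 g

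*Protocol*

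**What the plan says.** Protein is stated as an approximate 20 g per 500 ml in three places of the protocol.

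- Synopsis: "Each 500ml of milk provides about 20g of protein".
- Hypotheses, item 1: "Consumption of whole milk (2 × 500ml; 2 × ~20g protein) after a RE session twice a week".
- Data collection, Milk and control drink intake: "On average, 500ml milk contains ~20g of protein needed to stimulate muscle protein synthesis above stimulation provided by RE".

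That last section also gives the composition of the supplied products. It says that the "whole milk contains 3.6g fat, 3.4g protein, and 4.7g of carbohydrates per 100g of milk", and it gives the skimmed product 3.6 g protein per 100 g.

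Background and rationale describes a blunted response to protein in older adults, "especially to lower amounts of protein (EAA) of <20g (<10g) compared with young adults". It also gives general figures for whole milk: "6.3g/l (20%) of soluble whey proteins and 26g/l (80%) of insoluble caseins".

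On energy, Milk and control drink intake sets the control drink to match whole milk, taken as 66 kcal/100 g. Juice of 45 kcal/100 g "will be supplemented with 6.05g of maltodextrin (3.8kcal/g) per 100g of juice", or 30.25 g for 500 ml. Ethical considerations and risk and burden speaks of a small risk of "weight gain due to the consumption of 650 kcal from whole milk and control drink".

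**The concern.** One section both states a protein content and supplies the composition that contradicts it. The discrepancy would be trivial if 20 g were an arbitrary round number. Here it is the level at which the rationale is built: the Background ties a weaker response to amounts under 20 g, and the intervention section presents about 20 g as what is required. Rounding up moves the serving from below that level to on it.

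What is at stake is the description of the dose. The protocol lists dosage among the primary outcome measures and makes data for future research a primary aim. Compliance is actual over expected consumption, so a fully compliant participant would be described as receiving about 40 g of protein per session day. By the product figures that participant would have had about 34–35 g from whole milk or 36–37 g from skimmed. A main trial planned from the stated figure would start from the wrong dose.

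**Working it through.** **Inputs.** From Milk and control drink intake: 3.4 g (whole) and 3.6 g (skimmed) protein per 100 g; milk 66 kcal/100 g; juice 45 kcal/100 g; maltodextrin 6.05 g per 100 g juice at 3.8 kcal/g. From Background and rationale: 6.3 + 26 g/l protein for whole milk in general. From Ethical considerations and risk and burden: 650 kcal. Assumption: milk density 1.00 to 1.035 g/ml, which the protocol does not give.

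**Can the stated ~20 g be reproduced?** Protein per 500 ml = (g per 100 g) × 5 × density.

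| Product | Density 1.00 | 1.03 | 1.035 | Shortfall from 20 g |
|---|---|---|---|---|
| Whole, 3.4 g/100 g | 17.0 g | 17.5 g | 17.6 g | 12–15% |
| Skimmed, 3.6 g/100 g | 18.0 g | 18.5 g | 18.6 g | 7–10% |

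It cannot, for either product. Reaching 20 g in 500 ml would need 20 / 5 = 4.0 g/100 g at density 1.00, or 20 / (5 × 1.035) = 3.9 g/100 g at 1.035. No milk in the protocol has that.

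**Two servings.** Whole: 2 × 17.0 to 2 × 17.6 = 34.0–35.2 g. Skimmed: 2 × 18.0 to 2 × 18.6 = 36.0–37.2 g. The stated dose is 2 × ~20 = ~40 g.

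**General milk figures.** (6.3 + 26) / 2 = 16.15 g per 500 ml, 19% below 20 g. This is whole milk in general, not the study product. It gives no support to 20 g, but it does not belong in the study range.

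**Maltodextrin.**

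- Control drink as specified: 45 + 6.05 × 3.8 = 67.99 kcal per 100 g juice.
- Gram for gram against milk: 67.99 / 66 = 1.030, so 3.0% higher, or about 10 kcal per 500 g.
- By volume, with milk at 1.03 g/ml: 66 × 1.03 = 67.98 kcal/100 ml, and (67.98 − 45) / 3.8 = 6.05 g. The protocol's figure is reproduced if milk is converted to volume and 100 g of juice is taken as 100 ml. The 30.25 g for 500 ml (5 × 6.05) treats juice the same way.

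**650 kcal.** On that basis two servings of control drink give 2 × 5 × 67.99 = 680 kcal, and whole milk gives 10 × 67.98 = 680 kcal. This is 680 / 650 = 1.046, or 4.6% above the stated figure. With milk at 1.00 g/ml, whole milk is 660 kcal. From the product composition with assumed factors of 9, 4 and 4 kcal/g for fat, protein and carbohydrate, whole milk is 3.6 × 9 + 3.4 × 4 + 4.7 × 4 = 64.8 kcal/100 g, which is 648 kcal per 1,000 ml at 1.00 g/ml and 667 kcal at 1.03.

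**The case against.** The best defence is that the figure is openly approximate and drives nothing. The research questions define the intervention by volume, compliance is a ratio of consumption, and no sample size or analysis is computed from protein. The composition of both milks is printed, so anyone can work out what was delivered. The level in the Background is a summary of literature in comparison with young adults, not a threshold of this plan. The same section frames the evidence gap as more than 20 g per day after exercise, which two servings exceed. With 30 participants in three groups and no claim of power, 2–3 g of protein will not decide how the muscle measures are read.

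Much of this stands, and it limits the importance of the point. It does not remove the contradiction. The gap runs in one direction for both products, and it is larger for whole milk, which Hypothesis 1 names. The wording in the intervention section presents about 20 g per serving as needed, which is more than a loose descriptor.

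A reader might also infer that the control drink is not matched in energy to whole milk. The protocol does not support that. The maltodextrin figure is reproduced on a plausible volume basis, the drinks are served by volume, and no juice density is given from which a mismatch could be shown. What remains is that the basis is unstated. Nor is 650 kcal shown to be wrong for whole milk, since the product composition gives 648 kcal at density 1.00. It disagrees with the calculation behind the maltodextrin figure.

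**Conclusion.** The stated protein content is wrong by the protocol's own figures. A 500 ml serving of study milk gives 17.0–17.6 g (whole) or 18.0–18.6 g (skimmed), 7–15% below 20 g and always under it. This rests on the printed product composition and an assumed density of 1.00 to 1.035 g/ml; no density in that range changes the conclusion.

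The effect falls on the stated justification for the serving and on the description of the dose. A reader might go further and conclude that Hypothesis 1 is undermined. It is not: that hypothesis asks whether the intervention is feasible, and protein appears in it only in parentheses. Nor does the arithmetic say that the volume should change. The point is a cheap correction that is worth making, and it does not stand in the way of running the pilot.

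Secondary and minor: the mass/volume basis of the control drink calculation is unstated, and 650 kcal is about 30 kcal below the 680 kcal per session day which that calculation implies.

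**What to change.** Restate protein per 500 ml in the Synopsis, Hypothesis 1 and Milk and control drink intake, separately for whole and skimmed milk, from the product composition and with the density or other mass/volume basis given. Reconcile the result with the 20 g level in Background and rationale and with the wording that presents about 20 g as needed. How to reconcile them is for the investigators. Use the restated figures to describe the dose by arm in the report and in planning the main trial.

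In the same edit, state the mass/volume basis of the maltodextrin calculation for both milk and juice, and reconcile the 650 kcal in Ethical considerations and risk and burden with it.

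The cost is a short recalculation and wording changes in four sections, with the Background also touched if the reconciliation calls for it. The stated protein content becomes less favourable. Design, sample size and analysis are unaffected.
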